### Interim analysis

An interim analysis of efficacy will be performed when 75% of participants have been enrolled in the trial. The level of significance will maintain an overall P value of 0.05 and be calculated according to the O’Brien-Fleming stopping boundaries [29].

### Randomisation

A statistician, with no clinical involvement in the trial, will computer-generate a stratified (by anaesthetist) block randomised sequence. This list will remain concealed from the trial coordinator at all times. When the trial coordinator has assessed and enrolled a participant, she will telephone an independent person to obtain the treatment allocation. She will then inform the appropriate nursing and medical staff who will deliver the intervention(s). The trial coordinator will not collect outcome data, deliver the intervention(s), or provide patient care.

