## Method

### Trial design

The trial will employ a randomised 2 x 2 factorial design. An equal ratio of participants will be allocated to each group. This design will enable the study of each intervention on the outcome variable, as well as the effects of interactions between interventions on the outcome variable.

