### Setting

The trial will be conducted in the day surgery unit of a private hospital in Sydney, Australia.

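### The coordinator who enrols patients also receives and relays every allocation, so the next one can be guessed better than chance: a minor, conditional risk that rerouting one call would reduce

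*Protocol article*

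**What the plan says.** All the main facts are in the Randomisation section of the protocol article.

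- A statistician with no clinical part in the trial is to "computer-generate a stratified (by anaesthetist) block randomised sequence".
- On concealment, the section is explicit: "This list will remain concealed from the trial coordinator at all times".
- Enrolment comes first and allocation second. Once a patient has been judged eligible and entered by the coordinator, "she will telephone an independent person to obtain the treatment allocation". She then passes the allocation on to the staff who deliver the treatment.
- Her other duties are ruled out: "The trial coordinator will not collect outcome data, deliver the intervention(s), or provide patient care".

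Two other sections bear on how predictable the sequence is. Under Trial design, "An equal ratio of participants will be allocated to each group", so with four arms the smallest block is 4. Under Setting, there is one day surgery unit. Block size, and whether it varies, are not given. The Blinding section adds that the preoperative and intraoperative staff are each to be unaware of what the other group delivers.

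**The concern.** Concealment exists to stop the person who decides on entry from foreseeing the next allocation. Telephoning after enrolment protects the allocation of the patient just enrolled. It does not stop the allocations already made from informing whether the next patient is approached, enrolled or deferred.

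Here one person holds both pieces: the decision on entry, and the full history of allocations for each anaesthetist. Blocking forces the arms back into balance within an anaesthetist, so an arm that is behind is more likely to come next. By the article's own account she has no role in delivery, care or outcome collection, so she needs the allocation only as a messenger.

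At stake is selection at entry. Blinded outcome assessment and intention-to-treat analysis do not correct it.

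**Working it through.** The article gives no figure for predictability, so there is none to reproduce.

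**Inputs from the article.** Four arms in equal ratio; blocks within anaesthetist; N = 120; SD 0.5°C (Sample size section).

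**Assumptions.** Block sizes of 4, 8 and 12, and a random mix of them; five or six anaesthetists of equal load, so 120/5 = 24 or 120/6 = 20 patients per stratum; perfect recall of past allocations.

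**Step 1. Block of 4, by hand.** Each block holds two prewarmed and two not prewarmed patients. The chance that the best guess is right, by position, is:
- first: 1/2
- second: 2/3
- third: 1/3 × 1 + 2/3 × 1/2 = 2/3
- fourth: 1

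Mean g = (0.500 + 0.667 + 0.667 + 1)/4 = 0.708. Status is certain in (1/3 + 1)/4 = 33% of allocations. For the four-arm allocation, (1/4 + 1/3 + 1/2 + 1)/4 = 52%, against 25% by chance.

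**Step 2. Larger fixed blocks, size known, whole blocks (simulated).**

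| Block | Arm guessed | Prewarming guessed | Prewarming certain |
|---|---|---|---|
| 4 | 52% | 71% | 33% |
| 8 | 47% | 67% | 20% |
| 12 | 44% | 64% | 14% |

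**Step 3. Block size unknown.** The rule is to guess the level less used so far with that anaesthetist. Simulated with 8,000 replicates in strata of 20 to 24:

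| Blocks | Arm guessed | Prewarming guessed |
|---|---|---|
| 4 | 52% | 71% |
| 4 and 8 mixed | 48% | 67–68% |
| 4, 8 and 12 mixed | 45% | 65% |

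With fixed blocks, the running counts are equal at the end of every block, so this rule makes the same guess as someone who knows the size. Not knowing the size, or varying it, removes most of the certainty but leaves much of the guessing advantage.

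**Step 4. Stratum size.** With known blocks of 8, prewarming is guessed correctly 66.5% of the time in a stratum of 120, 64.6% in one of 20 and 59.9% in one of 6. Small strata leave unfinished blocks, and the late positions are the predictable ones.

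**Step 5. Illustrative bias.** Suppose each enrolment for which a guess is possible shifts the expected postoperative temperature by ±d SD in the guessed direction. The expected difference between prewarmed and not prewarmed patients is then 2d(2g − 1) SD. With 60 against 60, its standard error is √(2/60) = 0.183 SD.

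| Block (strata of 20) | g | d | Bias, SD | Bias, °C (× 0.5) | False positives |
|---|---|---|---|---|---|
| 4 | 0.708 | 0.25 | 0.21 | 0.10 | 20% |
| 8 | 0.646 | 0.25 | 0.15 | 0.07 | 12% |
| 4 | 0.708 | 0.10 | 0.08 | 0.04 | 7% |
| 8 | 0.646 | 0.10 | 0.06 | 0.03 | 6% |

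The false-positive rates come from simulation (6,000 replicates, six strata, no covariate adjustment). The normal approximation agrees: for the first row, 0.208/0.183 = 1.14, and P(Z > 1.96 − 1.14) is about 21%. The shift d is an assumption, and nothing in the article estimates it.

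**The case against.** The strongest case is that this is a sound, standard procedure. The sequence comes from an uninvolved statistician, the list is hidden, and each allocation is released by an independent person only after enrolment. Much of this stands.

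- **No contradiction.** A reader might infer that the list is revealed block by block, so that the promise of concealment at all times is false. The article does not support that. What is concealed is the list. What she learns is one allocation at a time, after the patient has been enrolled.
- **Block size.** A reader might also fault the article for not giving it. A condensed article may leave that to the full protocol, and varying, undisclosed blocks may already be in use. The point survives because step 3 does not need the size.
- **Small strata.** It is tempting to say that small strata make matters worse. At a given block size they do the opposite (step 4).
- **Little room to steer.** The eligibility criteria are largely objective: age, scheduled surgery, ASA grade, body mass index, temperature and language. Discretion lies mainly in whom she approaches. The planned adjustment for baseline temperature would absorb part of any steering on that variable.
- **Assumed shift.** At ±0.1 SD the error rates stay close to 5%. The larger figures need ±0.25 SD at every enrolment for which a guess is possible.
- **Her limited role.** Having no part in delivery, care or outcomes confines the harm to selection at entry. It also means that she does not need the information.

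What does not stand is the argument that predictability vanishes unless she knows the block size.

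**Conclusion.** The point holds as a minor, conditional risk. Two stated features, blocking within anaesthetist and routing every allocation through the person who enrols, let her guess the next patient's prewarming status correctly about 71% of the time with blocks of 4 and 65% with mixed blocks of 4, 8 and 12, against 50% by chance. These figures assume strata of about 20 to 24 and perfect recall, and fall in smaller strata.

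Harm needs a further step: she must act on the guess, knowingly or not. Its size then depends wholly on the assumed shift. The article gives no sign that steering is intended or likely, and the error rates above are no forecast. They should not be judged against the 0.05°C difference in the Sample size section either: with SD 0.5 that difference would need about 3,140 patients for a main effect, not 120, which is a separate matter.

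**What to change.** Reword the Randomisation section along these lines: once the coordinator has registered an enrolled patient with the independent person, that person gives the prewarming allocation directly to the preoperative team and the irrigation allocation directly to the operating-room team; the coordinator is not told either.

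This also secures the Blinding section's aim that neither team knows what the other delivers. The present wording is compatible with that aim but does not guarantee it.

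The cost is a reworded procedure and rerouted calls, with no new staff and no change to design, sample size or analysis. The change has to be in place before enrolment, since selection at entry cannot be undone later. There are two limits. The coordinator can no longer check delivery of the allocation herself, so someone else must. She may also still see 45 minutes of blanket warming in the holding area of a single unit, so the gain for prewarming is partial.

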### Blinding

Outcome measures will be collected by recovery unit nursing staff who are blinded to the participants’ treatment allocation. The two interventions will be delivered by separate groups of perioperative staff (preoperative and intraoperative staff) and each group will be blinded to the treatment delivered by the other. The trial will adhere to procedures to maintain separation between the recovery unit nursing staff who will record the outcome data and the preoperative and intraoperative nursing and medical staff who will deliver the intervention(s). Due to the difficulty in blinding participants to the preoperative warming intervention, they will be blinded to the trial hypothesis and design [30].

### Statistical analysis

Intention-to-treat analysis will be applied. Data will be analysed according to the 2x2 randomised factorial study design. The two-way analysis of covariance (two-way ANCOVA) will be used for the primary and secondary outcome measures of temperature, thermal comfort and total recovery time. The two-way ANCOVA model will also include operating room ambient temperature, volume of irrigation solution, length of surgery, blood loss and other covariates identified in the bivariate analyses. The analysis will be adjusted for baseline temperature and thermal comfort. Pair-wise comparison between groups will be conducted based on the results obtained from the two-way ANCOVA.

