**Method/Design:**

The trial will employ a randomised 2 x 2 factorial design. Eligible patients will be stratified by anaesthetist and block randomised into one of four groups: Group one will receive preoperative warming with a forced air warming device; group two will receive warmed intraoperative irrigation solutions; group three will receive both preoperative warming and warmed intraoperative irrigation solutions; and group four will receive neither intervention. Participants in all four groups will receive active intraoperative warming with a forced air warming device. The primary outcome measures are postoperative temperature, thermal comfort, and total recovery time. Primary outcomes will undergo a two-way analysis of variance controlling for covariants such as operating room ambient temperature and volume of intraoperative irrigation solution.

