## Background

Inadvertent perioperative hypothermia, defined as a core temperature below 36°C [1], is a common, yet widely under-acknowledged adverse clinical consequence of surgery [1-3]. Patients undergoing arthroscopic shoulder surgery are particularly at risk, with the average patient experiencing a core temperature heat loss of between 1°C and 3°C [4-6]. Three principle factors are said to contribute to this problem: Reduced metabolic heat production due to the anaesthetic; heat loss due to the cold perioperative environment and the use of large quantities of surgical irrigation solution; and impaired thermoregulation which results in a core to periphery thermal redistribution [7].

Although hypothermia is a common perioperative problem, it is not a benign one: The consequences are both physiological and psychological in nature and are far more serious than patients just ‘feeling uncomfortably cold’. Research has demonstrated a clear link between inadvertent perioperative hypothermia and serious adverse complications including myocardial ischaemia, surgical site infection, and coagulopathy [1,8-11]. A person’s temperature is also an integral component of their overall perception of well-being and research has shown that memories of thermal discomfort during the perioperative period significantly affect a patient’s surgical experience [12,13]. These physiological and psychological adverse effects can, and do, result in prolonged recovery times, lengthier hospital stays, and increased resource use which in turn translates into greater overall healthcare costs [10,11].

A number of active and passive interventions are recommended in the evidence-based guidelines for maintaining normothermia in perioperative patients [1,14]. Two relatively simple and inexpensive interventions which are not routinely used on patients undergoing shoulder arthroscopy surgery are preoperative warming using a forced air warming device and the use of warmed intraoperative irrigation solutions [7].

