### Warmed intraoperative irrigation solutions

It is well documented that the use of room temperature irrigation solution increases the risk of inadvertent perioperative hypothermia during arthroscopic surgery. A systematic review of 13 randomised controlled trials including 686 patients showed that room-temperature irrigation fluid caused a greater drop in core body temperature and more episodes of hypothermia in patients, than warmed irrigation fluid [4]. There is a significant correlation between the volume of room temperature irrigation solution used and a patients’ mean postoperative temperature [6,24]. The use of warmed solution for intraoperative irrigation during arthroscopic surgery has been recommended as a method for preventing perioperative hypothermia [1,4,14].

There is clear evidence that these two interventions assist in the maintenance of perioperative normothermia but there is now a call for robust well designed research to demonstrate improved clinical outcomes associated with their use [1]. This trial will study the effects of these warming interventions on outcomes of particular interest to perioperative nurses, namely, post-operative temperature, thermal comfort, and total recovery time.

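### The stated ANCOVA adjusts for irrigation volume, length of surgery and blood loss, which arise after randomisation, so it cannot be relied on to give each intervention's total effect

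*Protocol article*

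**What the plan says.** The Statistical analysis section names a single model. The two-way ANCOVA "will be used for the primary and secondary outcome measures of temperature, thermal comfort and total recovery time", and it "will also include operating room ambient temperature, volume of irrigation solution, length of surgery, blood loss", together with further covariates picked out by bivariate analyses. A separate sentence deals with pre-treatment values: "The analysis will be adjusted for baseline temperature and thermal comfort". The Abstract (Method/Design) repeats part of the covariate list, "controlling for covariants such as operating room ambient temperature and volume of intraoperative irrigation solution".

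Four other places bear on the point:

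- **Purpose:** the question is what the two interventions do, singly and together, to the three outcomes.
- **Randomisation:** the coordinator obtains the allocation at enrolment and passes it to the staff who will deliver the interventions. Allocation therefore precedes both.
- **Background:** perioperative hypothermia is linked to "serious adverse complications including myocardial ischaemia, surgical site infection, and coagulopathy".
- **Warmed intraoperative irrigation solutions:** there is a "significant correlation between the volume of room temperature irrigation solution used" and postoperative temperature.

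**The concern.** Randomisation balances the groups on whatever exists before allocation. It does not balance them within levels of something measured later. Adjusting for a later variable can do harm in two ways. If the intervention changes the variable and the variable changes the outcome, adjustment removes that part of the effect. If the variable and the outcome share a cause that is not in the model, such as case complexity, and the intervention also changes the variable, adjustment brings in a bias that the unadjusted comparison does not have.

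The headline estimates for all three outcomes are at stake. They would answer a narrower question than the one in the Purpose, and randomisation alone would no longer justify them.

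**Working it through.** **Step 1: timing and routes.** The three covariates, set against what the document says:

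| Covariate | When it arises | Route from intervention to covariate | Relation to temperature |
|---|---|---|---|
| Blood loss | During surgery | Indirect: hypothermia to coagulopathy (Background) | Not stated |
| Irrigation volume | During surgery | None stated | Stated, for room-temperature fluid |
| Length of surgery | During surgery | None stated | Not stated |

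All three follow allocation. All three also follow the 45 minutes of preoperative warming, and they build up while the warmed or unwarmed fluid is in use. Under Blinding, each staff group is kept unaware only of what the other group delivers. The intraoperative staff are therefore not blinded to the irrigation they deliver.

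**Step 2: when adjustment matters.** The plan has no figure of its own to reproduce here, so this step shows only how the distortion works. Take one covariate with unit variance within groups, and let

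- T = total effect of an intervention on temperature (°C);
- a = effect of the intervention on the covariate (SD);
- b = effect of the covariate on temperature (°C per SD);
- u and g = effects of an unmeasured common cause (unit variance) on the covariate (SD) and on temperature (°C).

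In a linear model the adjusted coefficient is T − a·b − a·g·u, so

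distortion = −a·(b + g·u).

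It is zero whenever a = 0, whatever b, g and u are.

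**Step 3: illustration.** Every input below is an assumption. T = 0.50°C is a round value, not the difference given under Sample size. The distortion does not depend on T.

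| a | b | g·u | Distortion (°C) | Adjusted estimate (°C) |
|---|---|---|---|---|
| 0 | −0.1 or −0.2 | 0 or −0.1 | 0 | 0.50 |
| −0.2 | −0.1 | 0 | −0.02 | 0.48 |
| −0.2 | −0.2 | 0 | −0.04 | 0.46 |
| −0.5 | −0.1 | 0 | −0.05 | 0.45 |
| −0.5 | −0.2 | 0 | −0.10 | 0.40 |
| −0.5 | −0.1 | −0.1 | −0.10 | 0.40 |
| −0.5 | −0.2 | −0.1 | −0.15 | 0.35 |
| −0.5 | 0 | +0.1 | +0.05 | 0.55 |

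Example, seventh row: −(−0.5)·(−0.2 − 0.1) = −0.15, and 0.50 − 0.15 = 0.35. A simulation of the 2×2 design (N = 120, 1,500 replicates per setting, g = 0.2 and u = 0 or −0.5) agreed with the first seven rows to within 0.003°C. The model without the covariate returned 0.50 throughout, to two decimals. The last row comes from the formula alone and shows that the sign can reverse.

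**The case against.** The strongest reply is that the plan may lose nothing. If neither intervention changes a covariate, adjusting for it leaves the total effect intact and may sharpen the estimate. The document says that irrigation volume goes with temperature, which makes volume prognostic. It does not say that warming alters volume or operating time. Even for blood loss the link is generic. The Background speaks of hypothermia at large, not of bleeding in shoulder arthroscopy, and all four groups are actively warmed during surgery, which may narrow the contrast. No section says that blood loss affects temperature. Intraoperative staff are also blinded to preoperative warming, so their knowledge of allocation could influence volume or duration only for the irrigation factor.

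All of that stands. It limits how much can be claimed, but it does not show that the covariates are unaffected, and blinding does not block a physiological route.

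A reader might infer more than the document supports in four respects:

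- **That the model fails to estimate the total effect.** This needs an effect of allocation on a covariate, and none is shown.
- **That intention-to-treat is breached.** "Intention-to-treat analysis will be applied" concerns analysing patients as allocated, and covariates reassign nobody. The issue is which effect is estimated.
- **That a common volume slope for warmed and unwarmed fluid is misspecified.** The article does not say whether covariate-by-factor terms enter, and a condensed account may leave that to a fuller plan.
- **That a definite amount of power is lost.** That needs an invented mediated share, and it ignores the residual variance the covariates may remove.

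Nor is the lack of a stated baseline-only analysis a fault in itself, since a fuller plan may contain one. The point rests on what the article says the model will include.

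**Conclusion.** The concern holds in a limited form. The one model stated for all three outcomes conditions on three variables that arise after randomisation and after preoperative warming. For blood loss the document itself supplies a possible route from the intervention. For volume and duration it shows only the timing and, for the irrigation factor, delivering staff who are not blinded to it. The adjusted estimate therefore cannot be relied on to give the total effect sought in the Purpose.

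The size is unknown. Under the assumptions tabulated above, the distortion runs from none, through losses of 0.02 to 0.15°C, to a gain of 0.05°C. These figures show the mechanism and are not forecasts for this trial. Whether any distortion exists depends on a, for which the document gives no value. A primary model should not need a to be zero when a model free of that condition is available.

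The point does not extend to baseline temperature and comfort, which are sound covariates. Nor does it extend to room ambient temperature, which the document gives no reason to think allocation would change.

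**What to change.** State the primary ANCOVA as the two factors, their interaction, the anaesthetist stratum, the T0 value of the outcome where one exists (temperature and thermal comfort, but not total recovery time), and only those further covariates that are named in advance and known before randomisation. The open-ended addition of covariates found in bivariate analyses should not bring post-randomisation variables back into this model.

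Report the model with irrigation volume, length of surgery and blood loss as a supportive analysis. Label it as adjusted for intraoperative variables, and do not present it as the effect of using the interventions. Bring the Abstract's wording into line.

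This changes analysis text only. No data collection, sample size or trial conduct is affected. The downside is a possible loss of precision, to the extent that the three variables explain variance in the outcomes. The change should be made before outcome data are seen by allocation, which includes the planned interim efficacy analysis.

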### Outcomes

The primary outcome measure in this trial is postoperative temperature. The secondary outcomes of interest are thermal comfort and total recovery time. Baseline data on patient temperature and thermal comfort will be collected on arrival into the department (T_0_). Follow-up measures will be collected at four time points; immediately prior to induction (T_1_), on arrival into the recovery unit (T_2_), 20 minutes after arrival into the recovery unit (T_3_) and immediately prior to discharge from the recovery unit (T_4_) (see Figure 1).

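### Bivariate screening lets the trial data choose part of the primary ANCOVA, and nothing limits the candidates to variables measured before randomisation

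*Protocol article*

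**What the plan says.** The Outcomes section of the protocol article states: "The primary outcome measure in this trial is postoperative temperature". The Statistical analysis section says that a two-way ANCOVA "will be used for the primary and secondary outcome measures of temperature, thermal comfort and total recovery time". That model is to include "operating room ambient temperature, volume of irrigation solution, length of surgery, blood loss" "and other covariates identified in the bivariate analyses". The section then adds: "The analysis will be adjusted for baseline temperature and thermal comfort".

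The text shown gives no list of candidates, no selection rule and no restriction to variables measured before randomisation.

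On timing, the Outcomes section describes baseline data as "collected on arrival into the department (T_0"). It continues: "Follow-up measures will be collected at four time points; immediately prior to induction (T_1_), on arrival into the recovery unit (T_2"), followed by two later recovery readings. T1 is thus classed as follow-up. The Interventions section places the 45 minutes of forced-air warming in the preoperative holding area, so for the two groups that receive it T1 is read after that treatment.

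The Interim analysis section adds: "An interim analysis of efficacy will be performed when 75% of participants have been enrolled in the trial". That is 0.75 × 120 = 90 patients.

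**The concern.** Two things are at stake.

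First, the clause makes part of the primary model depend on the data it will be used to test. The two factors, four named covariates and two baseline measures are fixed, but the remainder is unknown until the data have been examined.

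Second, the clause does not keep out variables that treatment may already have changed. A reader cannot assume that the further covariates will be baseline ones, because three of the four named ones (irrigation volume, length of surgery, blood loss) can be known only after randomisation. T1 temperature shows what could go wrong. It is an earlier reading of the primary outcome with the same thermometer, so it is likely to correlate with postoperative temperature, and it follows the preoperative warming. The Purpose section asks for the effect of that warming on postoperative temperature. A model that conditions on T1 estimates only the part of the effect not already present at induction.

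**Working it through.** The protocol gives no figure on this point to reproduce. It also gives no correlation between readings and no expected effect at T1, so the sizes below are illustrations with assumed inputs.

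**1. A post-treatment covariate**

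Inputs from the protocol: 120 patients and equal allocation, hence 30 per cell and 60 v 60 for each main effect.

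Assumed inputs: total preoperative warming effect 0.25°C; share *s* of that effect already present at T1; T0 with SD 0.5; and

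- T1 = 0.6·T0 + *a*·warm + noise (SD 0.4), with *a* = *s* × 0.25 / 0.7
- T2 = 0.7·T1 + *c*·warm + 0.25·irrigation + noise (SD 0.35), with *c* = (1 − *s*) × 0.25

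The model with T0 only estimates 0.7*a* + *c* = 0.25°C. Adding T1 leaves only *c* = (1 − *s*) × 0.25°C.

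Check of power with T0 only: the SD of T2 given T0 and treatment is √(0.7² × 0.4² + 0.35²) = √0.2009 = 0.448. The standard error is 0.448 × √(2/60) = 0.0818. Then 0.25/0.0818 = 3.06, and Φ(3.06 − 1.96) = Φ(1.10) = 86%. Simulation (3,000 trials per scenario) gave 85-86%.

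Results after adding T1:

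| Share of effect present at T1 | *c* by formula | Simulated estimate | Simulated power |
|---|---|---|---|
| 0% | 0.25 | 0.25 | 97% |
| 25% | 0.1875 | 0.19 | 82% |
| 50% | 0.125 | 0.12 | 46% |
| 75% | 0.0625 | 0.06 | 15% |
| 100% | 0 | 0.00 | 5% |

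In the 0% row power rises, because T1 then acts purely as a strong predictor of T2. Under these inputs T1 passed a bivariate screen at p < 0.05 in every simulated trial.

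A second set of assumptions (warming raises T1 by 0.3°C, slope of T2 on T1 0.6, remaining effect 0.07°C; 4,000 trials) sends 0.6 × 0.3 = 0.18°C of the 0.25°C through T1, a share of 0.18/0.25 = 72%. The estimate fell from 0.25 to 0.07°C and power from 87% to 14%, in line with the 75% row.

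**2. Selecting baseline variables from the data**

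Assumed: no preoperative warming effect, 120 patients, 5, 10 or 20 baseline candidates of which two predict the outcome, residual SD 0.5, 3,000 trials. The simulation error at a rate of 5% is √(0.05 × 0.95/3000) = 0.4 percentage points.

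- One fixed cut-off (0.01, 0.05, 0.10, 0.20 or 0.25): type I error 4.8-5.2%.
- Most favourable of six models (no covariates, or any of the five cut-offs): 7.7% with 5 candidates, 8.6% with 10, 8.9% with 20.

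A variant with 10 candidates, three of them prognostic, gave 5.7% at a fixed 0.10 cut-off and 8.4% for the best of six cut-offs.

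**The case against.** The strongest reply is that the protocol never says T1 will be a covariate. It labels T0 as the baseline, lists T1 as follow-up, and says that the temperature adjustment is for baseline. All of that is correct. A reader might infer that the plan will adjust away the preoperative warming effect, but the documents do not support that. They show only that nothing prevents a variable such as T1 from entering.

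A related reply concerns size. The protocol's Background (Preoperative warming) describes the benefit as a smaller fall after induction and quicker recovery during surgery. That points to a modest share at T1, so a fall in power from 87% to 14% should not be read as the expected result. It is one assumed point towards the unfavourable end of the range. This stands.

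A reader might also infer that the screen is repeated for each outcome and at each look. Neither the Interim analysis nor the Statistical analysis section says so, and a covariate set chosen once would fit the text equally well. What can be said is that the text does not fix one model across looks.

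Nor does screening in itself inflate type I error to any important degree. The inflation needs an open cut-off and a favourable choice among models, a practice the protocol does not describe.

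Last, candidate lists and cut-offs are often left to an analysis plan, which is not shown here. That would answer a complaint of missing detail. It does not answer this one, because the article positively states that covariates found in bivariate analyses will be in the model used for the primary outcome.

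**Conclusion.** The point holds as a fault in a stated rule. Part of the primary model is to be chosen from trial data, and the wording admits post-treatment variables. The harm depends on what enters. If T1 did, a true preoperative warming effect of 0.25°C would be estimated at anything from 0.25 to 0.00°C, with power from 97% to 5% against about 86% with T0 only. The result turns on the unknown share of the effect present at T1, and on the assumed slopes and SDs. If only baseline variables enter at one fixed cut-off, type I error stays near 5%; with an open cut-off and the most favourable model reported, it could reach about 8-9%. The documents do not show that any of these losses will occur. They show that the plan does not exclude them, and a change of wording would.

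**What to change.** In the Statistical analysis section, delete the screening clause from the primary model. Name any further covariates in advance, all measured before randomisation. They should include anaesthetist, the stratification factor given under Randomisation, alongside the T0 temperature and thermal comfort already planned. Total recovery time has no T0 value, so use the same baseline covariates for it. State that the same prespecified model will be used for a given outcome at the interim and final analyses. Report screened or extended models only as sensitivity analyses.

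The cost is wording, plus one real loss: a baseline predictor discovered in the data cannot enter the primary model. Other baseline variables, such as age, body mass index or ASA grade, are optional and this point does not depend on them. Whether the four named intraoperative covariates should stay is a separate question that this change does not settle.
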